### Data Analysis

#### Qualitative Data

All interviews will be audiotaped, transcribed, and identified using an alphanumeric log. A thematic analysis will be conducted using the RQDA (R package for the qualitative data analysis) software (version 2.15.2; 2012-10-26). A total of 2 junior (JT and AR) postdoctoral health psychologists and 1 senior (AB) postdoctoral health psychologist will code the transcripts. The analysis of thematic content will allow both the frequencies of responses for each category to appear and the meaning of the responses associated with each category to emerge [92,93]. A coding grid will be constructed from 2 complementary processes; (1) a pre-established code based on the research objectives and the semidirected interview guide will be elaborated to create broad coding categories and subcategories, and (2) a third of the interviews will be coded, using an emergent coding method, to test and modify the grid. Following an iterative process, several rounds of analysis will be conducted to stabilize the coding sheet. Finally, double interjudge and intrajudge coding will be conducted to ensure the reliability and independence of coding.

A similar content analysis will be performed for focus group interviews, with coding based on themes related to the content, format, and clinical implementation guidance of the QPL.

#### Quantitative Data

Statistical analyses will be conducted using SPSS software (version 27.0; IBM Corp). Standardized questionnaires used in steps 1b and 2, and the Delphi surveys, will be analyzed descriptively in terms of missing data, response frequency, mean and SD, median, and range.

In step 1b, responses to items of the PTPQ, EORTC QLQ-INFO25, and SCNS-SF34 will determine the prevalence of communication needs in the cancer resistance setting and thus help prioritize communication issues to compose the QPL.

The step 1b group (QPL naive) will comprise a historical control of patients from step 2 (QPL intervention group). Quantitative data collected from standardized questionnaires at step 1b will be compared with the data collected at step 2. Patients will be consecutively included in steps 1b and 2; therefore, they are expected to be clinically similar; however, sociodemographic and clinical data between these groups will be compared to check their similarity. Bivariate analyses of outcome measures will be performed to preliminarily assess the potential clinical usefulness of the QPL. Bivariate analyses will also be performed to explore patients’ satisfaction with information and support needs in relation to their sociodemographic and psychological characteristics (distress and coping strategies) in step 2 samples, overall and by cancer site.

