In addition, patients with advanced cancer do not participate as much as they wish during consultations [8,13]. Possible explanatory factors include patients forgetting questions, doubting the legitimacy of asking, expressing concerns indirectly, fear of the possible pejorative answer, and a lack of physicians encouraging their questions [14-16]. Patients may also present different needs and expectations, which depend on the time in their disease course [17] or factors such as their attentional coping style or sociodemographic background [10,18,19]. Discordance between the patient’s and oncologist’s perception of treatment aims and the disease timescale may result in medical decisions that do not align with life goals that are important to patients [20,21]. This leads to patients’ greater psychological distress [22].

Patient-centered communication is the cornerstone of high care quality [23]. This allows physicians to better respond to patients’ information and support needs. To this end, guidelines to improve communication skills of health care professionals are available in many countries [24-28]. Effective physician-patient communication may decrease patients’ anxiety, sustain hope [29], and increase satisfaction with care [30-32]. Patient-focused communication aids have also been developed to complement physician communication skills training [18,30-32]. These interventions are designed to enhance patients’ participation in the consultation and thus may increase physicians’ awareness and timely accommodation of their needs and expectations [33-36].

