##### Quantitative Assessment

Standardized questionnaires will be completed by patients to describe their unmet information and support needs while facing cancer resistance in the MBC and MUM settings. These questionnaires will also be used to obtain preliminary data, albeit limited to the potential clinical usefulness of the designed QPL. This will be performed by comparing responses from patients at step 1b (QPL-naive group) with clinically similar patients at step 2 (QPL intervention group).

As information needs may depend on patients’ characteristics [10,18], these outcomes will be assessed according to patients’ sociodemographic (ie, age, gender, educational level, and marital status) and psychological correlates (ie, beliefs, preference for information, level of distress, and coping strategies). To address these outcomes and correlates, patients will be invited to complete standardized questionnaires, as detailed in Table 3.

**Table 3 table3:** Standardized questionnaires.

Measures of QPL^a^ potential clinical benefits			Factors assessed

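### The step 1b versus step 2 contrast is unadjusted, and consecutive inclusion does not make two recruitment periods comparable, so prognostic differences could be mistaken for a QPL effect

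*Protocol article*

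**What the plan says.** The Quantitative Data section of the protocol article sets the control: "The step 1b group (QPL naive) will comprise a historical control of patients from step 2 (QPL intervention group"). It gives the ground for comparability: "Patients will be consecutively included in steps 1b and 2; therefore, they are expected to be clinically similar". It then adds a safeguard: "sociodemographic and clinical data between these groups will be compared to check their similarity". The outcome analysis follows: "Bivariate analyses of outcome measures will be performed to preliminarily assess the potential clinical usefulness of the QPL". No covariate, stratification, matching or weighting is named for this contrast, and nothing is said about what follows if the groups differ.

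Elsewhere the article treats patient characteristics as important for the outcomes. The Background section says patients may have "different needs and expectations, which depend on the time in their disease course". The Quantitative Assessment section of step 1b says: "As information needs may depend on patients’ characteristics [10,18], these outcomes will be assessed according to patients’ sociodemographic" and psychological correlates. In the analysis section, however, those correlates are used only in separate bivariate analyses of satisfaction and needs, "in relation to their sociodemographic and psychological characteristics (distress and coping strategies) in step 2 samples, overall and by cancer site". They do not enter the step 1b versus step 2 contrast.

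**The concern.** Taking patients consecutively limits selection within a recruitment window. It does not make one window like the next. Step 1b enrols from January 2021 for one year. Step 2 needs QPL version 1, so it can begin only after the focus groups and the two-round Delphi.

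Eligibility spans the first three treatment lines after resistance. Step 2 admits both consultations that disclose resistance and follow-up consultations, in no fixed proportion. The mix of lines, disease duration, education and consultation type can therefore shift between steps.

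The abstract says clinical utility is assessed by this comparison, and the sample-size paragraph says the data are to prepare further randomised trials. It is the only between-group estimate of what the QPL does. If case mix shifts on factors that drive information and support needs, the unadjusted difference carries that shift into the planning of the next trial. The Discussion names the cross-sectional design as a limitation, but not confounding from a non-concurrent control.

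**Working it through.** **The plan's own figure.** Table 2 gives 40 patients per tumour site in each step: 40 + 40 = 80, which agrees with the text. No alpha, power, effect size or SD is stated, so nothing further can be reproduced.

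**What each safeguard covers.**
- Consecutive inclusion: selection within a period, not differences between periods.
- Same eligibility criteria in both steps: the range of patients admitted, not their distribution within that range (three lines, any time since metastasis).
- Site quotas of 40 and 40: tumour site, if the quotas are met in both steps.
- Similarity check on sociodemographic and clinical data: detects a difference at best, with no stated action.

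**How sensitive the check is.** Assume a two-sided 5% test of two proportions (the article states no level). With p̄ the mean of the two proportions and n the number per group:

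SE0 = √(2p̄(1 − p̄)/n); SE1 = √((p1(1 − p1) + p2(1 − p2))/n); power = Φ((|p2 − p1| − 1.96 × SE0)/SE1).

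For 50% versus 65%, p̄ = 0.575:
- n = 80: SE0 = √(0.48875/80) = 0.0782; SE1 = √(0.4775/80) = 0.0773; power = Φ((0.15 − 0.1532)/0.0773) = Φ(−0.041) = 0.484.
- n = 40: SE0 = 0.1105; SE1 = 0.1093; power = Φ((0.15 − 0.2166)/0.1093) = Φ(−0.610) = 0.271.

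The same formula over a range of true imbalances:

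| Imbalance | 80 vs 80 | 40 vs 40 (one site) |
|---|---|---|
| 50% vs 60% | 24% | 14% |
| 50% vs 65% | 48% | 27% |
| 50% vs 70% | 74% | 44.5% |

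**What an uncorrected imbalance would do.** Bias in SD units = imbalance × effect of the factor on the outcome. Neither is given in the article, so both are assumed.
- 15-point imbalance, factor worth 0.5 to 1.0 SD: 0.15 × 0.5 = 0.075 SD to 0.15 × 1.0 = 0.15 SD.
- 20-point imbalance, same factor: 0.10 to 0.20 SD.

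For scale, the unadjusted mean difference at 80 versus 80 has SE = √(2/80) = 0.158 SD and a 95% CI half-width of 1.96 × 0.158 = 0.31 SD. The 15-point case moves the estimate by 0.075/0.31 = 24% to 0.15/0.31 = 48% of that half-width.

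**The case against.** The best defence is that the article claims little for this contrast. It calls the data preliminary and limited, assesses only potential usefulness, and looks ahead to randomised trials. It plans a similarity check, uses the same eligibility criteria in both steps and sets equal site quotas. What follows an imbalance could be laid down in a full protocol or SAP that is not shown. All of this stands, and it limits the weight of the point. It does not repair the inference from consecutive inclusion to similarity, nor the stated choice of a bivariate outcome analysis.

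A reader might infer more than the article supports:
- *That any case-mix difference will be read as a QPL effect.* Only differences on prognostic factors bias the contrast, and the planned check could expose a large one.
- *That tumour-site mix is a confounder.* Table 2 balances it by quota. The 39 and 28 completed questionnaires at the end of October 2021 were counted while the planned enrolment year was still running, so they do not show a missed quota.
- *That the false-positive rate is inflated.* A bias of 0.075 to 0.15 SD would raise a 5% test to 7.6% to 15.8%, but the article states no alpha and no significance decision for this contrast.
- *That adjustment would narrow the interval by √(1 − R²).* This holds only when covariates are unrelated to group, and the worry here is that they are related. The variance factor is (1 − R² of outcome)/(1 − R² of group on covariates). With both at 0.10 it is 0.90/0.90 = 1, which is no gain.
- *That everything needed is already collected.* The step 1b Overview does not list treating oncologist, date of resistance or consultation type.

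**Conclusion.** The point holds as a worthwhile, low-cost improvement to a pilot's utility aim, not as an error in a confirmatory test. The article specifies an unadjusted comparison with a non-randomised, non-concurrent control, and justifies it by an argument that does not establish comparability. Its own text says the outcomes depend on patient characteristics and on time in the disease course.

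The planned check is too insensitive to settle the matter: about 48% power for a 15-point imbalance at 80 versus 80, and 27% at 40 versus 40. These figures rest on an assumed two-sided 5% level and a starting proportion of 50%. The bias figures rest wholly on assumed imbalances and prognostic effects. They show what could happen, not what will. Adjustment would address measured factors only.

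**What to change.** Make the main step 1b versus step 2 contrast a regression of each outcome scale on group, adjusted for a small prespecified set of pre-consultation factors: cancer site, treatment line, time since metastatic diagnosis, age and education. Add consultation type (disclosure or follow-up) if it is recorded in both steps. Report the adjusted difference with its 95% CI and the unadjusted difference beside it. Keep results by site descriptive or minimally adjusted, because 40 versus 40 will not carry the full set.

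Do not adjust for HADS or for PTPQ beliefs. They are measured together with the outcomes and could themselves be affected by the QPL. Leave out treating-oncologist effects, since that variable is not listed as collected.

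Replace the inference from consecutive inclusion to clinical similarity with a statement that unmeasured and calendar-time confounding remains.

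**Cost.** The listed clinical and sociodemographic data supply age, education and date of metastasis, and treatment line should be derivable from previous and current treatments. The change is therefore mostly wording, plus recording consultation type. It uses a few degrees of freedom and may lose some precision if covariates are imbalanced between groups.

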#### Step 1b: Patients’ Communication Experience and Information and Support Needs in the Oncology Consultation Dealing With Treatment Resistance

##### Overview

A cross-sectional assessment of patients’ communication needs in the context of cancer resistance will then be performed. Patient enrollment started in January 2021 and will take place over 1 year.

Consecutive patients will be identified via lists of oncology consultation agendas in an oncology center (Institut Curie, Paris). If they respond to the inclusion and exclusion criteria listed in Textbox 1, they will be invited to participate in the study.

Patients’ sociodemographic data (age, gender, educational level, and marital, parental, and professional status) and clinical data (date of initial diagnosis, disease recurrence and metastatic occurrence, stage, previous and current disease-targeted treatments, and supportive care interventions) will be collected from patients or medical records to describe the study population.

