As indicated in Table 2, a sample size of 80 patients (40 patients by tumor site) is planned. Sample sizes up to 40 per group are expected to provide estimates that are precise enough to assess the feasibility of QPL use and obtain preliminary clinical data for further randomized controlled trials of this tool [89].

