### Step 2: QPL and Implementation Pilot Testing

The second step of the study pilot tests the QPL version 1 for its acceptability, feasibility, potential clinical utility, and sustainability. Consecutive patients (n=80) responding to the same eligibility criteria as in step 1b will be recruited. They will receive the QPL version 1 to prepare their subsequent oncology consultations, either a consultation during which the diagnosis of cancer resistance is communicated or in the course of a new disease-targeted treatment follow-up consultation. They will be invited to complete the same standardized questionnaires as in step 1b.

Additional questions will address the QPL acceptability in terms of uptake (the QPL has been read before the consultation), use (QPL items have been raised during the consultation), and patients’ and clinicians’ perceived helpfulness and satisfaction with this tool and its use in clinical practice.

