Third, the quantitative assessment allows the assessment of the specific information and support needs that are experienced when faced with cancer resistance. These data may be compared between 2 groups: before (step 1b) versus after (step 2) the availability of the QPL. This will offer initial information on the clinical utility of the tool tailored to cancer resistance in the French cultural context.

Owing to consecutive sampling, information will be available about the number of patients willing to use the QPL and the number of oncologists who will engage in its use during consultations [92]. Furthermore, the resulting QPL will be pilot-tested on outcomes such as patients’ beliefs about primary cancer treatment goals or satisfaction with the information provided about prognosis and treatment, which are important [93] and previously lacking effect measurement of QPL use [2].

Finally, focus group discussions will specifically elicit collaborative work. The reactions and proposals of various appropriate persons [100] will help prepare the modalities of QPL use in routine practice and promote its long-term adoption [101], that is, the tool use in real-world clinical practice [102]. Moreover, the Delphi process aims to reach consensus among patients and oncology professionals on a QPL version 1 and explicit guidance for clinical implementation [103,104]. We anticipate that these persons will have diverging views and opinions about the tool [91]; thus, a consensus will have to be developed.

This protocol has several limitations. The methodology described herein is an innovative but long process. It may not be systematically applied as a new clinical context in need of a QPL. However, this study offers the opportunity to reveal unnecessary steps and thus indicate an optimized process for future research.

We focus on the communication between oncologists and patients; however, other oncology professionals such as nurses or psychologists may also play an important role in responding to patients’ information and support needs; therefore, further research is needed to address their specific role in addressing these needs. In addition, patients’ relatives may also present their specific information and support needs and may interact with the patient when facing this information. The QPL may also be useful to them, as such or adapted, and this must be evaluated.

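### The treating oncologist is absent from the stated step 1b versus step 2 comparison, so a change in oncologist mix could not be told apart from a QPL effect

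*Protocol article*

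**What the plan says.** Under Data Analysis, Quantitative Data, step 1b serves as the historical control for step 2, and "Bivariate analyses of outcome measures will be performed to preliminarily assess the potential clinical usefulness of the QPL". Comparability is expected because inclusion is consecutive, and "sociodemographic and clinical data between these groups will be compared to check their similarity". No oncologist term, stratum or clustering allowance is mentioned. Nor is any confidence interval, test or significance level.

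On recruitment, the Step 1b Overview says "Consecutive patients will be identified via lists of oncology consultation agendas in an oncology center". The sociodemographic and clinical items listed there do not include the treating oncologist. For step 2 the protocol says "Consecutive patients (n=80) responding to the same eligibility criteria as in step 1b will be recruited"; it does not restate the centre.

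On size, "a sample size of 80 patients (40 patients by tumor site) is planned" for step 1b, and Table 2 gives the same split for step 2. The justification is that "Sample sizes up to 40 per group are expected to provide estimates that are precise enough to assess the feasibility of QPL use".

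On the oncologist's part, Step 1c describes a PTPQ item as rating the quality of treatment information that came from the oncologist. Principal Findings expects to report "the number of oncologists who will engage in its use during consultations". The Dissemination section refers to studies in which endorsement by clinicians encouraged patients to use such a tool.

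**The concern.** Patients taken from consultation agendas are grouped by the oncologist they saw. Where an outcome partly rates that oncologist, or where use of the list depends on that oncologist's engagement, patients of the same oncologist tend to resemble one another. Two things follow.

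- **Confounding.** The two groups are enrolled in different periods. If oncologists who communicate better supply a larger share of step 2 than of step 1b, outcomes improve without any contribution from the QPL. A bivariate comparison cannot separate the two, and the planned similarity check would not reveal the shift.
- **Precision.** Estimates from a single step (prevalence of unmet needs in step 1b, uptake and use in step 2) carry less information than the same number of independent patients would. Step 1b prevalences feed a 50% rule for prioritising QPL content. The comparison and the feasibility estimates are meant to inform later randomised trials.

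**Working it through.** **Inputs.** From the protocol: 80 patients per step, 40 per tumour site. It gives no alpha, power, effect size, SD or precision target, so the sample size cannot be reproduced; it rests on a cited rule of thumb. It also does not give the number of oncologists, their caseload, the ICC, or their overlap between steps. Assumed here: K = 4, 8 or 12 oncologists per step with equal caseloads m = 80/K, ICC = 0.01, 0.05 or 0.10, and overlap from complete to none.

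**1. Benchmark under independence.** The 95% half-width for a 50% proportion is 1.96 × √(0.25/80) = 11.0 points (15.5 points at n = 40). The detectable difference at two-sided 5% and 80% power is (1.96 + 0.84) × √(2/80) = 0.44 SD (0.63 SD at 40 per step).

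**2. Bias from a change in mix.** Bias = shift in share × gap between oncologist groups. A 20-point shift with a 0.5 SD gap gives 0.20 × 0.5 = 0.10 SD. Over shifts of 10 to 30 points and gaps of 0.2 to 0.5 SD, the bias runs from 0.10 × 0.2 = 0.02 SD to 0.30 × 0.5 = 0.15 SD.

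**3. Single-step proportions.** Design effect (DE) = 1 + (m − 1) × ICC; half-width = 1.96 × √(0.25 × DE/80).

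- K = 8, ICC 0.05: DE = 1 + 9 × 0.05 = 1.45; effective n = 80/1.45 = 55; half-width 13.2 points instead of 11.0.
- Mildest case (K = 12, ICC 0.01): DE = 1.06; half-width 11.3 points.
- Most severe case (K = 4, ICC 0.10): DE = 1 + 19 × 0.10 = 2.90; half-width 18.7 points.

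**4. Step 1b versus step 2.** Let w1 and w2 be an oncologist's share of patients in each step, and c the part of the oncologist effect that is stable across periods. Then

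Var(difference) = (1 − ICC) × 2/n + ICC × [c × Σ(w1 − w2)² + (1 − c) × (Σw1² + Σw2²)].

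Dividing by the independence variance 2/n gives the variance ratio VR. The true error of a nominal 5% test is 2 × (1 − Φ(1.96/√VR)).

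| Overlap of oncologists | VR with equal caseloads | VR, K = 8, ICC 0.05 | VR, full range | True error, full range |
|---|---|---|---|---|
| Same oncologists, equal shares, stable effects | 1 − ICC | 0.95 | 0.90–0.99 | 3.9–4.9% |
| Same oncologists, 20% of effect varies by period | 1 + (0.2m − 1) × ICC | 1.05 | 1.00–1.30 | 5.0–8.6% |
| Half replaced, stable effects | 1 + (m/2 − 1) × ICC | 1.20 | 1.02–1.90 | 5.3–15.5% |
| All replaced | 1 + (m − 1) × ICC | 1.45 | 1.06–2.90 | 5.7–25.0% |

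So a patient-level analysis of the contrast is slightly conservative under full, balanced and stable overlap. It becomes anti-conservative as oncologists change or as their effects vary by period.

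**The case against.** The strongest reply is that the article specifies no interval and no test, so there are no stated error bars to be wrong. It is also a condensed account: a clustering term or one more coded field is the kind of detail often left to the full protocol or SAP, neither of which is shown. This stands. A reader might infer that the plan's intervals are wrong, but the article does not support that. The precision results above apply only if patient-level intervals or tests are used.

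A reader might also infer that oncologist mix will in fact be taken for a QPL effect. Nothing in the article shows that the mix shifts. Consecutive inclusion, the same eligibility criteria and the same 40/40 split by tumour site in both steps make overlap plausible. The single centre is stated for step 1b and only inferred for step 2. In the cases tried, the bias of 0.02 to 0.15 SD is well below the detectable 0.44 SD.

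Not every outcome depends on the oncologist. The psychological needs scale covers matters such as anxiety and uncertainty, and uptake means having read the list before the consultation. The comparison is also labelled preliminary.

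What remains is narrower. The article does commit to a bivariate comparison with a non-concurrent control. It names the variables for the similarity check, and the oncologist is not among them. Consecutive sampling does not ensure that the same oncologists contribute equal shares in two periods. It is also hard to see how the promised count of engaged oncologists could be produced without identifying them.

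**Conclusion.** The point holds as a cheap improvement to an exploratory comparison. Under the stated method, a difference in oncologist mix between the two periods cannot be distinguished from a QPL effect. Unless the oncologist is recorded, nobody can later say whether such a difference existed. The illustrative bias of 0.10 SD is modest, and it is conditional on a 20-point shift in mix and a 0.5 SD gap, both assumed.

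For single-step proportions, patient-level intervals, if given, would be too narrow for any positive ICC, with a design effect of 1.06 to 2.90 at n = 80 over the assumed range. For the contrast between steps the direction is not fixed in advance: VR is 0.90 to 0.99 with the same oncologists in equal shares and stable effects, and up to 2.90 if all are replaced. All these sizes rest on assumed oncologist numbers, equal caseloads, assumed ICCs and assumed overlap.

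**What to change.** - Record a coded treating oncologist with every questionnaire in steps 1b and 2. For step 1b patients already enrolled, the code should be retrievable from the agendas used to identify them.
- Report the oncologist mix in each step beside the sociodemographic and clinical comparison.
- Show an oncologist-stratified estimate (oncologist as fixed effect) of the step 2 versus step 1b difference beside the bivariate one.
- If intervals are given for step 1b prevalence or for step 2 uptake and use, allow for clustering by oncologist, with a small-sample correction if oncologists are few.

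The cost is one coded field and one model term. Intervals will be somewhat wider, and oncologists seen in only one step add no information to the stratified estimate. If few oncologists take part in both steps, the stratified estimate will be weak, and the report should say so. Stratification also leaves other changes between the two periods unaddressed.

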**Objective:**

This study aims to develop and pilot-test a specific QPL in the following two contrasting clinical contexts in France after cancer resistance has developed: triple-negative and luminal B metastatic breast cancer (MBC) and metastatic uveal melanoma (MUM).

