### Objective

We propose an original design for the development of a complex intervention based on the Medical Research Council framework [74].

The specific aims are (1) to develop the content of a QPL for adults diagnosed with resistant cancer, who are still eligible for disease-targeted treatment, and (2) to pilot-test the implementation of this intervention in oncology consultations in a French cancer setting. During this process, the implementation will be prepared by investigating potential obstacles and facilitation strategies from the outset.

We expect to obtain a core QPL comprising questions and concerns that patients in the treatment resistance context might generally want to express at the oncology consultation. A common *core* QPL will be complemented with subsections containing specific issues for either the triple-negative and luminal B MBC or the MUM cancer sites.

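### The step 1b versus step 2 outcome comparison is planned with no role for cancer site, although recruitment is fixed at 40 per site in each step

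*Protocol article*

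**What the plan says.** All references are to the Protocol article.

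- **Comparison.** The Quantitative Data section sets step 1b (no QPL, historical control) against step 2 (QPL) on the standardized questionnaires. The method is given as "Bivariate analyses of outcome measures will be performed to preliminarily assess the potential clinical usefulness of the QPL". Cancer site is not mentioned.
- **Where site does appear.** The following sentence describes another analysis, relating satisfaction and needs to patient characteristics. It is to be done "in step 2 samples, overall and by cancer site".
- **Sample.** Under Step 1b, Quantitative Assessment, "a sample size of 80 patients (40 patients by tumor site) is planned", with the reasoning that "Sample sizes up to 40 per group are expected to provide estimates that are precise enough to assess the feasibility of QPL use". Table 2 repeats 40 MUM and 40 MBC for each step. Step 2 states only the total: "Consecutive patients (n=80) responding to the same eligibility criteria as in step 1b will be recruited".
- **Aim and tool.** The Abstract's objective is to "pilot-test a specific QPL in the following two contrasting clinical contexts in France". The Objective section expects a common core "complemented with subsections containing specific issues for either the triple-negative and luminal B MBC or the MUM cancer sites".
- **Status.** Both the Step 1b and the Quantitative Data sections describe the comparison as preliminary.

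**The concern.** Site is built into the design in three ways: as an eligibility criterion, as a recruitment quota and as an expected feature of the tool. The one analysis meant to speak to the QPL's clinical usefulness does not use it, while a secondary exploration in the next sentence does. A bivariate comparison most naturally means step against outcome, with no third variable.

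Two things are at stake. First, readers of the pilot may be given one overall difference and nothing for each cancer, although the two were chosen because they differ in prognosis and treatment options. A difference present in one site only would be diluted. Second, an overall contrast that ignores site depends on the MBC/MUM mix being the same in both steps. If it is not, part of any between-site difference in information or support needs is counted as a QPL effect. Ignoring site also leaves between-site variation in the error term.

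**Working it through.** **What can be reproduced.** The plan gives no alpha, power, effect size or SD, so there is no sample size calculation to repeat. The totals agree: 40 + 40 = 80 per step.

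**Assumptions for what follows.** Outcomes in SD units (SD = 1), two-sided 5% level, normal approximation. The effect sizes and between-site differences are illustrative, since the documents give none.

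**1. Shift from unequal site mix.** The Results section reports 39 MBC and 28 MUM questionnaires completed at 31 October 2021, while enrollment was still open.
- MBC share in step 1b at that count: 39/67 = 0.582.
- MBC share in step 2 if the quotas are met: 40/80 = 0.500.
- Shift in the unadjusted contrast = (0.582 − 0.500) × between-site outcome difference = 0.082 × that difference.
- Between-site differences of 0.2, 0.5 and 0.8 SD give shifts of 0.016, 0.041 and 0.066 SD.
- With 40/40 in both steps the shares are equal and the shift is 0.

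**2. Precision.** The 95% half-width of a difference between steps is 1.96 × √(1/n₁ + 1/n₂).
- Overall, 80 v 80: 1.96 × √(2/80) = 0.31 SD.
- One site, 40 v 40: 1.96 × √(2/40) = 0.44 SD.
- MUM, if step 1b stayed at 28: 1.96 × √(1/28 + 1/40) = 0.48 SD.
- Difference between sites in the step effect: 1.96 × √(4/40) = 0.62 SD.

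**3. What one overall figure can hide or gain.**

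| Assumed true effect | Overall, 80 v 80 | One site, 40 v 40 |
|---|---|---|
| 0.6 SD in one site, 0 in the other | averages to 0.3 SD, power 0.48 | power 0.77 in the site with the effect |
| 0.5 SD in both sites | power 0.88 | power 0.61 |

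The overall figure does worse in the first case and better in the second, so both are worth reporting.

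**4. Variance left in by ignoring site.** With an equal split and a between-site mean difference of d within-site SDs, the variance is multiplied by 1 + d²/4 and the interval by its square root.
- d = 0.2: √1.01 = 1.005, about 0.5% wider.
- d = 0.6: √1.09 = 1.044, about 4% wider.
- d = 1.0: √1.25 = 1.118, about 12% wider.

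**The case against.** The strongest reply is that the article is silent on site and does not choose against it. It never says that the two cancers will be combined. A bivariate analysis can be run within each site, and a condensed article may leave such reporting to a fuller document. The sample size wording, "Sample sizes up to 40 per group are expected to provide estimates that are precise enough", placed beside 40 per tumor site, could even mean that the site within each step is the intended unit of estimation. The common core is the main product and is expected to apply in other advanced cancers, so an overall difference is a legitimate target. The comparison is openly preliminary and historically controlled, and the illustrative effects are not the plan's own.

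Much of this stands. That the sites will be combined is an inference from the word bivariate and from the contrast with the next sentence; it is not stated. A reader might also infer that every MBC and MUM patient gets a different tool. The Objective section and Step 1c foresee site-specific parts, but the Discussion makes them conditional on need.

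The reply does not remove the point. The article does give site-level detail, but attaches it to the lesser analysis. Stratifying by a quota variable that is already collected guards against a drift in site mix and removes between-site variance. The preliminary status argues for estimates with intervals; it is no reason to leave site out.

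**Conclusion.** The point holds in a limited form. The usefulness comparison is described with no role for cancer site, so the plan does not commit to showing the difference in each of its two contexts. Its overall contrast is also unprotected against a change in site mix.

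The size is modest. The shift is 0.082 times the between-site outcome difference if step 1b ended at 39 and 28 against 40 and 40, and nil if the quotas are filled. The 39/28 count is an interim status and not a forecast. The widening from ignoring site runs from negligible to about 12% over assumed site differences of 0.2 to 1.0 SD.

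A reader might infer that the pilot cannot say anything about either cancer. The documents do not support that. Site is known for every patient, the same questionnaires are planned for 40 per site in both steps, and by-site estimates are available without changing the design. Step 2 also collects uptake, use and perceived helpfulness. The larger limit on any claim that the tool helps is the non-randomized historical control, which by-site reporting does not cure.

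**What to change.** In the Quantitative Data section, state that each step 1b versus step 2 outcome difference will be:

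- estimated overall with cancer site as a stratum or adjustment term (for example, a linear model with step and site); and
- reported separately for MBC and for MUM, with 95% confidence intervals, as descriptive estimates.

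Any comment on usefulness in one cancer should rest on that cancer's own estimate and be labelled preliminary. Settle this before step 2 data are examined, so that by-site results are not picked afterwards.

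The cost is a sentence or two of text and slightly more tabulation, with no extra patients, data or change in sample size. The by-site intervals will be wide and cannot reliably separate the two sites, so a difference between the MBC and MUM estimates should not be read as evidence that the tool works in one and not the other.
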